#### Subproject B

Subproject B is an analysis of post-intervention effects on muscle fibres or muscle tissue components in older adults. This exploratory sub-study will analyse muscle tissue from 60 participants to generate hypotheses on potential effects of reducing SB on muscle tissue. The muscle biopsy will be performed at week 21 (after assessing the post-intervention activity level with accelerometers) from a biopsy specialist and biomarkers will be assessed (Myostatin, IL-8, IL-15, VEGF, BDNF, FGF21, irisin, Type 2/Type 1 fibre ratio, Wnt and Notch signalling, CDC42). In this exploratory analysis, the physical activity profile or the sedentary profile from baseline assessment and of the post-intervention period, respectively, will be used as a main exposure marker to be analysed in relationship to the various biomarker measurements. Beside descriptive and summary measures we will use a multivariable analysis approach to quantify the relationship, and simultaneously adjusting for potential confounders such as age, gender and co-morbidities.

### Process evaluation

SITLESS follows the guidance on ‘Process evaluation of complex interventions’ from the Medical Research Council (MRC) for conducting the process evaluation of the study [59]. It was applied in the feasibility study to understand the feasibility of the recruitment strategy and of the SMS intervention and, hence, optimise its design and evaluation for the full trial.

The process evaluation of the full trial will be coordinated by a non-intervention site and is aimed at providing greater confidence in conclusions about effectiveness of the intervention by assessing: (1) the quantity and quality of what was delivered (implementation) regarding the PA and the SMSs interventions; and (2) the generalisability by understanding the role of context. Moreover, the process evaluation will help to understand the mechanisms of impact.

All intervention sites will combine their findings to gain a greater understanding of how the SMSs and the PA interventions are implemented and the extent to which they work. Methodologically, basic quantitative measures of implementation such as fidelity and adherence will be combined with qualitative data, including observation on sessions, focus groups and interviews with a purposeful sample of participants with different profiles. Moreover, the sessions on monitoring and support of the SMSs instructors will be used to gather further information on implementation challenges. Research teams will provide context information on each intervention site.

Qualitative and quantitative findings will be triangulated according to a standardised protocol that will entail: (1) sorting themes and following threads; and, where relevant, (2) seeking convergence, complementarity, silence and dissonance in themes, looking for either full or partial agreement or disagreement across the methods [60]. Our methods will follow best practice reporting guidelines for qualitative studies [61].

### Data and statistical analysis

The full analysis set will follow the intention-to-treat principle and will include all randomised participants for whom a baseline assessment is conducted, regardless of later temporary or permanent loss to follow-up, withdrawal or drop-out of the study.

The study hypothesis will be tested with mixed linear models with repeated measures, to assess changes in main outcomes (SB and CPM) over time (T0 to T3) and between-study arms. A diagonal matrix design will be considered for the within-participants covariance matrices (covariance structure for repeated measures factors). Fixed effects in the analyses will be treatment group and country (study site), the latter based on its relevance as proxy for intervention and cultural differences. Random effects may be considered for the ERS + SMS group and ERS group, to take into account within-study clustering. A diagonal matrix design will be considered for the between-participants covariance matrices (covariance structure for random factors). The between-participants correlations induced by randomisation by centre and the clustering of cohabiting individuals will be taken into account in the models. Further testing of the study hypotheses will be conducted through covariance analyses, including in the model relevant covariates (age, gender, BMI, SPPB level and frailty), and effect modifiers.

Secondary analyses will be conducted to explore changes over time in the relative efficacy of the interventions. Mixed linear models with repeated measures will be built to assess changes over time between intervention groups in main and secondary variables, at baseline (T0) and T1, T2 and T3. Interaction terms between treatment and time will be considered to test for differences over time between treatments.

A sensitivity analysis will be conducted, restricted to the ‘per protocol’ dataset, comprising all participants with no protocol violations and complete (e.g. no missing data) measurements for the primary variables for all study assessments (baseline, end of treatment, first follow-up, second follow-up). A second sensitivity analyses will be conducted for any primary variable with a substantial number of missing values (higher than 5%), imputing missing data by the ‘last observation carried forward’ method.

No subgroup analyses are planned in advance. Any subgroup analysis conducted will be treated with caution and output will be treated as exploratory rather than definitive. Missing data will be imputed through a multiple imputation approach, imputing missing values with the corresponding average values from the set of participants in the control group in the same country as the participant, matched for age, gender, baseline PA and baseline SPPB score.

Two-sided tests of statistical significance will be used in all statistical analyses. Estimates of the size of treatment effects will be presented together with confidence intervals, in addition to significance tests. Significance levels will be set to a 5% level, applying the Bonferroni correction to adjust for type I error criteria. All analyses will be performed with SPSS version 20 or Stata version 12.

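### As written, the primary repeated-measures model pairs a diagonal within-participant covariance with no stated participant random effect, so one person's four measurements would be treated as uncorrelated

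*Protocol article*

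**What the plan says.** All of this stands in the protocol article, Data and statistical analysis.

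- Model, covering T0 through T3 and differences between arms: "The study hypothesis will be tested with mixed linear models with repeated measures, to assess changes in main outcomes (SB and CPM) over time (T0".
- Covariance between visits: "A diagonal matrix design will be considered for the within-participants covariance matrices". A parenthesis in the text assigns this to the repeated-measures factor, so it is the matrix linking the four visits of one person.
- Fixed effects: "Fixed effects in the analyses will be treatment group and country (study site").
- Random effects: "Random effects may be considered for the ERS + SMS group and ERS group, to take into account within-study clustering". These are optional, and none is named for the control arm.
- Covariance of the random effects: "A diagonal matrix design will be considered for the between-participants covariance matrices (covariance structure for random factors").
- Other dependence: "The between-participants correlations induced by randomisation by centre and the clustering of cohabiting individuals will be taken into account in the models".
- Treatment by time, listed under the secondary analyses: "Interaction terms between treatment and time will be considered to test for differences over time between treatments".

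Under Study design, month 22 is named as the main assessment.

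**The concern.** A diagonal matrix for the repeated factor lets the variance differ between visits but fixes every covariance between visits at zero. That is harmless only if a random effect at person level, or one that acts like it, carries the correlation instead. The section names none. Its random terms concern the two exercise arms, and the other correlations it undertakes to model (centre, cohabitees) are between participants. The only sentence about covariance within a person sets it to zero.

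Accelerometer counts and sedentary time measured four times on the same older adult can be expected to correlate positively. Ignoring this makes the standard error too small for an arm effect averaged over visits (false positives) and too large for a change from baseline (lost power). The section leaves both contrasts open as the primary test. The listed fixed effects, with treatment by time appearing only as secondary, point to the averaged effect. The stated aim of assessing change over time points to the change contrast.

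**Working it through.** **Inputs.** From Sample size: difference 30 CPM, SD 139, two-sided 0.05, power 80%, dropout 24%, 446 per arm. From Outcome assessment: four measurements. Assumed, because the protocol does not give it: a common within-person correlation ρ between any two visits, taken as 0.3 to 0.8. Also assumed: equal variance at each visit and complete data on 446 × 0.76 = 339 per arm.

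**The plan's own figure.** n per arm = 2 × [139 × (1.960 + 0.842) / 30]² = 337. Then 337 / 0.76 = 443.4, so 444 per arm and 1332 in total (445 per arm with the t distribution). The stated 446 and 1338 reproduce to within 1%. This calculation compares two means and does not use the repeated-measures covariance, so the present point leaves it untouched.

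**Arm effect averaged over the four visits.** The true variance of a person's mean is σ²(1 + 3ρ)/4. The diagonal model takes σ²/4. The true SE is therefore √(1 + 3ρ) times the model SE, and the actual type I error is 2[1 − Φ(1.96/√(1 + 3ρ))].

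**Change from T0 to T3.** The true variance of a person's change is 2σ²(1 − ρ). The diagonal model takes 2σ². The true SE is √(1 − ρ) times the model SE.

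- Model SE of the arm difference in change = 139 × √2 × √(2/339) = 15.10.
- True SE = 15.10 × √(1 − ρ) = 10.68, 9.55 and 6.75 at ρ = 0.5, 0.6 and 0.8.
- Power with the correct SE = Φ(30/true SE − 1.96).
- Power with the diagonal SE = Φ[(30 − 1.96 × 15.10)/true SE]. The numerator is only about 0.4, which is why the power stays just above one half whatever ρ is.

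| ρ (assumed) | Averaged effect: true/model SE | Averaged effect: type I error | Change: true/model SE | Change: type I error | Power, correct SE | Power, diagonal SE |
|---|---|---|---|---|---|---|
| 0.3 | 1.38 | 15.5% | 0.84 | 1.9% | 66% | 51% |
| 0.5 | 1.58 | 21.5% | 0.71 | 0.6% | 80% | 52% |
| 0.6 | 1.67 | 24.1% | 0.63 | 0.2% | 88% | 52% |
| 0.8 | 1.84 | 28.8% | 0.45 | <0.1% | 99% | 52% |

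**Simulation.** At ρ = 0.6, with three arms of 339 and 4000 runs, the type I error under the diagonal matrix alone was 0.235 for the averaged effect and 0.003 for the change contrast. With a participant intercept the averaged effect came back to 0.048.

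**Comparison at T3 alone.** SE = 139 × √(2/339) = 10.68 whatever ρ is, because no covariance between visits enters it. An unadjusted month-22 comparison is therefore essentially unaffected.

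**The case against.** The strongest reply is that the text does not say the measurements are independent. It says that a diagonal matrix will be considered, which is not final. It calls the model a mixed model, provides a covariance structure for random factors, and commits to modelling the clustering of cohabitees. If that clustering is handled with a household intercept, then for everyone enrolled singly this is a participant intercept, and a diagonal residual matrix beside it is a legitimate model under exchangeable correlation. The article is also condensed, and a full list of random effects may stand in a statistical analysis plan that is not shown.

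This limits the point without removing it. The harm is conditional on no such term being fitted. But the section does not say how cohabitee clustering will be modelled, and it describes that clustering as between participants. Diagonal is the only within-person structure it names. The article has stated a choice here, so this is not merely a detail left for later.

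Several stronger inferences are tempting, and the document does not support them:

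- *That the trial's p-values are wrong.* They would be wrong only if the text were followed literally.
- *That every primary comparison is affected.* Month 22 is the main assessment, and an unadjusted comparison there is not.
- *That correcting the covariance gains more than the table shows.* A baseline-adjusted comparison would reach about 94% power at ρ = 0.6 (SE 10.68 × √(1 − 0.36) = 8.54), but the step from 88% to 94% comes from baseline adjustment, not from the covariance.
- *That the handling of dropout collapses.* The plan relies on imputation for missing data, and the merit of that is a separate question.
- *That the diagonal structure for the random factors is a second error.* It only makes the variance components independent of one another.

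**Conclusion.** Wrong as written. The one structure named for within-participant covariance sets the correlation between visits to zero, and no stated term restores it. The sizes rest on an assumed exchangeable correlation, equal variances, 339 evaluable per arm and an unadjusted two-sided 0.05. On those terms, at ρ from 0.5 to 0.8, the averaged arm effect is tested at a true level of roughly 21% to 29%, and the T0 to T3 contrast loses between 28 and 47 percentage points of power. Even at ρ = 0.3 the level for the averaged effect is about three times nominal. The Bonferroni correction that the section plans does not repair this, because it moves the significance threshold and leaves the standard errors as they are. The conclusion lapses if the analysis in fact includes a participant intercept, and largely lapses with a household intercept. The plan should say so if that is the intention.

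**What to change.** In Data and statistical analysis, and in the statistical analysis plan, do one of the following:

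- Replace the diagonal structure for the repeated-measures factor with an unstructured 4x4 within-participant covariance. State the fallback in advance if it does not converge: heterogeneous Toeplitz, then heterogeneous AR(1).
- Keep the diagonal residual matrix and state explicitly that the model includes a participant random intercept. This is valid if the covariance is about the same between all pairs of visits. The unstructured matrix does not need that condition.

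The diagonal structure for the random factors can stay. The cost is one or two sentences. An unstructured matrix has 4 × 5 / 2 = 10 parameters, which about 3 × 339 = 1017 evaluable participants estimate easily. Sample size, visits and data collection are unchanged. At submission fewer than 250 participants had been included and none had completed the intervention (Trial status), so at that stage the change could be made well before any analysis.

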## Methods/design

### Study design

The present study protocol describes a multi-centre pragmatic three-armed parallel RCT. Outcomes will be assessed at baseline, month 4 (end of intervention), month 16 (12 months post intervention) and month 22 (18 months post intervention) which will be the main outcome assessment. The study protocol has been developed based on the Standard Protocol Items: Recommendations for Interventional Trials (SPIRIT) guidelines [34]. The study design was approved by the Ethics and Research Committee of each intervention site: The Ethics and Research Committee of Ramon Llull University (Fundació Blanquerna, Spain), The Regional Committees on Health Research Ethics for Southern Denmark (University of Southern Denmark, Denmark), Office for Research Ethics Committees in Northern Ireland (ORECNI) (Queen’s University of Belfast) and the Ethical Review Board of Ulm University (Ulm, Germany). Participation is voluntary and all participants will be asked to sign informed consent before the start of the study (see Additional file 1).

SITLESS, as a Responsible Research and Innovation project, has created guidance for the involvement of stakeholders in the project from the onset. Accordingly, four local advisory boards were created, one on each intervention site (Barcelona, Odense, Belfast, Ulm) and are periodically involved in the study. They comprise primary healthcare and sport professionals, older adults, policy-makers and other local stakeholders of relevance (e.g. health insurance, where relevant). A gender expert linked to the European project EGERA is part of the advisory board of Barcelona.

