### Sample size

A sample size of 1338 participants (randomised to one of three groups of 446 participants) will be needed to detect a moderate effect size of 30 daily counts per minute (CPM) in a two-sided test, at a power of 80% and an α of 0.05, a common standard deviation of 139 of the mean and a 24% dropout rate. A change of 30 CPM is considered a measurable moderate effect size in this population, assessed with ActiGraph GT3X+, and 139 is the standard deviation for CPM found in the literature [37]. The present sample size allows estimation of overall efficacy.

Sample size computations were conducted with online software GRANMO (http://www.imim.es/ofertadeserveis/software-public/granmo/; last accessed on 21/7/2014).

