### Randomisation and blinding

During the first meeting, a researcher will explain the trial to interested individuals, give them an information sheet about the study and obtain their written informed consent (see Additional file 1). Participants will then be scheduled for the baseline testing session. After the baseline assessment, each participant will be centrally randomised to one of the three study groups (e.g. ERS + SMS, ERS or the control group), using a computer-based random-block randomisation scheme, clustering by couples when cohabitees wish to be enrolled together. Concealed randomisation will be conducted centrally at FSiE, after each participant has been included in the study, assigned an identification code and has completed the study baseline assessment.

The trial has an open design with blind assessment of outcomes. Researchers conducting the baseline assessments will be blind to group allocation. The statistician will also be blind to group allocation until completion of the statistical analysis. Participants will be asked not to reveal group allocation when undergoing follow-up measurements, as researchers conducting follow-up measurements will be blind to group allocation. To assess the extent to which blinding has been preserved, researchers will record the number of cases in which allocation was revealed.

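### The primary hypothesis test, as described, estimates an arm difference pooled over all visits including baseline and does not isolate month 22, the declared main assessment

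*Protocol article*

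**What the plan says.** Study design in the protocol article lists four assessments and singles out "month 22 (18 months post intervention) which will be the main outcome assessment". The aim, at the end of the Background, is likewise framed as long term, at 22 months.

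Data and statistical analysis then tests the study hypothesis with mixed linear models with repeated measures, "to assess changes in main outcomes (SB and CPM) over time (T0 to T3) and between-study arms". The same paragraph states: "Fixed effects in the analyses will be treatment group and country (study site"). Neither time nor treatment-by-time is listed. The covariates for further testing are age, gender, BMI, SPPB level and frailty.

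The next paragraph opens: "Secondary analyses will be conducted to explore changes over time in the relative efficacy of the interventions". It is there that the article says "Interaction terms between treatment and time will be considered to test for differences over time between treatments". No section names a month-22 between-arm contrast as the primary test.

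On timing, Randomisation and blinding says "After the baseline assessment, each participant will be centrally randomised to one of the three study groups", so T0 is measured before allocation.

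**The concern.** A mixed model that has treatment but no treatment-by-time term fits one arm difference common to all visits in the response. Here the response includes T0, where randomisation makes the true difference zero. The coefficient tested therefore blends a pre-randomisation visit, an end-of-programme visit and two follow-up visits, whereas the declared target is the last of these alone.

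The pattern over time matters in this trial. The Background says that gains from exercise referral are rarely sustained, and the trial asks whether self-management strategies change that. A pooled test cannot separate an early effect that fades from an effect that lasts, and it shrinks a lasting effect by including baseline. A significant or non-significant primary result would then not answer the 22-month question.

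**Working it through.** **Inputs from the Sample size section.** The trial is sized "to detect a moderate effect size of 30 daily counts per minute (CPM) in a two-sided test", with SD 139, two-sided α 0.05, power 80%, 24% dropout, and 446 per arm (1338 in total).

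**Reproducing the plan's figure.**
- n per arm = 2 × (139/30)² × (1.960 + 0.842)² ≈ 337.
- Allowing for dropout: 337/0.76 = 443.4, rounded up to 444 per arm, or 1332 in total. The t-based version gives 338, and 338/0.76 = 444.7, so 445 per arm.
- Both agree closely with 446 and 1338. The sample size is not in error. It is a comparison of two means at a single time point, which fits a month-22 contrast and not a visit average.

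**What the treatment coefficient estimates.** With weights w₀ to w₃ that sum to 1, the expected coefficient is w₀·0 + w₁·δ₁ + w₂·δ₂ + w₃·δ₃, where δ₁, δ₂ and δ₃ are the true arm differences at T1, T2 and T3. The weights are equal if the visit variances are equal and the data complete, and inverse-variance under a diagonal covariance with unequal variances. Adding a main effect of time removes the common trend but still leaves a single arm difference across visits. With equal weights, for assumed profiles:

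| Arm difference at T0, T1, T2, T3 (CPM) | Averaged effect | Month-22 effect |
|---|---|---|
| 0, 30, 30, 30 | 90/4 = 22.5 | 30 |
| 0, 0, 0, 30 | 30/4 = 7.5 | 30 |
| 0, 45, 15, 0 | 60/4 = 15 | 0 |
| 0, 60, 30, 0 | 90/4 = 22.5 | 0 |

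The first and last rows give the same averaged effect although their month-22 effects are 30 and 0.

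**Power, two arms compared, 338 evaluable per arm.**
- SE at one visit = 139 × √(2/338) = 10.69.
- Averaged test under compound symmetry with visit correlation ρ, variance correctly estimated: SE = 10.69 × √((1 + 3ρ)/4).
- Baseline-adjusted month-22 contrast: SE = 10.69 × √(1 − ρ²).
- Unadjusted month-22 contrast: z = 30/10.69 = 2.81, power 80% whatever ρ is.

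The document gives no ρ, so a range is assumed. The true effect is a sustained 30 CPM, which is 22.5 for the averaged test:

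| ρ (assumed) | SE, averaged | Power, averaged | SE, adjusted month 22 | Power, adjusted month 22 |
|---|---|---|---|---|
| 0.3 | 7.37 | 86% | 10.20 | 84% |
| 0.5 | 8.45 | 76% | 9.26 | 90% |
| 0.7 | 9.41 | 67% | 7.64 | 98% |

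**Chance that the fading 0, 45, 15, 0 profile is declared positive.** At ρ = 0.6 the averaged SE is 8.95, z = 15/8.95 = 1.68, and power is about 39%. At ρ = 0.3 it is about 53%, and at 0.7 about 36%. The Bonferroni correction mentioned in the article would lower these figures.

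**The case against.** The fixed-effects sentence may not be a complete model equation. It can be read as saying which factors are fixed, since random effects follow directly, and the sentence before it speaks of change over time, which needs a time term. The Abstract describes the test as change from baseline to month 22 and between arms, so a contrast of the T0-to-T3 change might be intended. This is a condensed article, and exact model terms are commonly left to an analysis plan.

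Part of this stands. A reader might infer that the model contains treatment and country and nothing else, but the article does not say the list is closed. The point does not need that reading, because a time main effect would leave the treatment coefficient averaged. Nor is the point about missing detail: the article places treatment-by-time under exploratory secondary analyses and says only that it will be considered. A T0-to-T3 change contrast is not stated anywhere and fits badly with that placement, since such a contrast is itself a treatment-by-time term.

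A reader might also fault the absence of the baseline outcome from the covariate list. Because T0 is part of the response, that absence is not an error in itself. A longitudinal model with a common T0 mean also keeps T0 as a response.

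**Conclusion.** The concern holds: the hypothesis test as described does not isolate the month-22 difference that the design declares to be the main assessment. This follows from the stated terms and from randomisation after baseline, and it needs no assumed correlation. With equal weights a sustained effect is diluted by 25%, from 30 to 22.5 CPM. Unequal variances would change the weights but would not single out month 22.

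Two stronger conclusions are tempting but unsupported.
- A reader might infer that a fading effect will produce a positive primary result. It can but need not: the 45, 15, 0 profile has about 39% power at an assumed correlation of 0.6.
- A reader might infer that the averaged test always loses power. At an assumed correlation of 0.3 it has 86%, more than the month-22 contrast either unadjusted (80%) or baseline-adjusted (84%). The loss appears at higher correlations, and every gain above 80% comes from baseline adjustment, not from targeting month 22.

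The power figures assume equal visit variances, compound symmetry and a correctly estimated variance. The article says "A diagonal matrix design will be considered for the within-participants covariance matrices", so they are not the operating characteristics of that model taken literally.

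**What to change.** In Data and statistical analysis, define the primary model with treatment, time, treatment-by-time and country. Either enter the T0 value of the outcome as a covariate with T1 to T3 as responses, or keep T0 as a response with the arms constrained to a common T0 mean. Name the month-22 between-arm contrast as the primary test, and report the month-4 and month-16 contrasts from the same model as secondary.

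The cost is a change of wording in the protocol and any analysis plan. Data, software and sample size stay as they are: 338 evaluable per arm already gives about 80% power for 30 CPM at month 22 before any baseline adjustment. Trial status reports fewer than 250 participants enrolled and none through the intervention when the article was submitted, so at that point the change could be made before outcomes were known.

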### Study interventions

A complex intervention [38] consisting of a PA program with self-management strategies (ERS + SMS) will be delivered in primary care or community settings in urban areas of Barcelona (Spain), Odense (Denmark), Belfast (UK) and Ulm (Germany) (see Table 1). All trainers in charge of conducting both intervention groups will undergo a standardised training.

**Table 1 Tab1:** General information of the ERS and SMS interventions

Name of the program	Program components	Training responsible	Duration	General structure of each session
ERS intervention	Aerobic training. Strength-based/ endurance exercises. Balance-based functional exercises. Flexibility exercises.	Specially trained PA specialist: physical therapist; sport professional/trainer; ergotherapist with specific health qualification. Sessions will be always performed under the supervision of the same trainer.	16 weeks. Two sessions per week of 45–60 min. Ask each participant to perform a third session on their own such as a 30-min walk. The intervention will be conducted in an indoor primary-care or sports facility. Municipality facilities (e.g. activity centres for older adults).	All training sessions will begin with a 5–10 min warm-up focusing on social and physical interactions. Followed by 35 min of different exercises adapted to each individual’s functional level (according to the participants’ SPPB score^a^). All training sessions will end with cool-down (breathing exercises and stretching for 5–10 min.

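### Clustering by exercise class or trainer in the two active arms is left optional in the model and is absent from the sample size, so the stated 80% power holds only if participants are independent

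*Protocol article*

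**What the plan says.** The Data and statistical analysis section treats two kinds of clustering differently. For centre and couples it commits: "The between-participants correlations induced by randomisation by centre and the clustering of cohabiting individuals will be taken into account in the models". For the two active arms it only permits: "Random effects may be considered for the ERS + SMS group and ERS group, to take into account within-study clustering". It does not say whether the cluster is the exercise class, the trainer or something else. Country (study site) is a fixed effect.

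On delivery, Table 1 under Study interventions says of ERS: "Sessions will be always performed under the supervision of the same trainer". The same table gives SMS to the same specialist, and the ERS + SMS sessions section describes six group-based SMS sessions.

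The Sample size section states: "A sample size of 1338 participants (randomised to one of three groups of 446 participants) will be needed", for a difference of 30 CPM, "in a two-sided test, at a power of 80% and an α of 0.05", with "a common standard deviation of 139 of the mean and a 24% dropout rate". It mentions no ICC, class size or design effect.

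**The concern.** People who train together under one trainer, and who discuss goals and barriers as a group, may end up more alike than people in different classes. Table 1 lists social influence and social support among the SMS components, so some within-group similarity is an intended mechanism. Classes within one city can still differ from each other, so neither the site fixed effect nor the adjustment for couples removes this correlation.

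The plan as written allows the term to be left out. Standard errors for comparisons involving the active arms would then be too small whenever the within-class correlation is positive. ERS+SMS versus ERS, a stated aim of the trial, is the most exposed because both arms may be clustered. If the term is included, the test is sound but the trial has less power than the Sample size section claims.

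**Working it through.** **Inputs from the protocol article (Sample size section).** Difference 30 CPM, SD 139, two-sided α 0.05, power 80%, dropout 24%, 446 per arm.

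**Inputs assumed, because the documents give none.** Class size at enrolment m = 10 to 15; ICC = 0.01, 0.02 or 0.05; separate classes in ERS and ERS+SMS; equal clustering in both arms.

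**Step 1: reproduce the stated size.** n per arm = 2 × [139 × (1.960 + 0.842) / 30]² = 337 analysed. 337 / 0.76 = 443.4, so 444 enrolled per arm and 1332 in total. The t-based version gives 338 analysed, 445 per arm and 1335 in total. The stated 446 and 1338 are within two participants per arm, so there is no room for a hidden design effect.

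**Step 2: power claimed, under independence.** 446 × 0.76 = 339 analysed per arm. SE = 139 × √(2/339) = 10.68. Power = Φ(30/10.68 − 1.96) = 80.2%.

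**Step 3: add clustering, ERS+SMS versus ERS.** The SE in step 2 is after dropout, so the class size must be too: m′ = 0.76 × m, which is 7.6 to 11.4.

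- Design effect: DE = 1 + (m′ − 1) × ICC
- Type I error if clustering is ignored: 2 × [1 − Φ(1.96/√DE)]
- Power if clustering is modelled: Φ(30/(10.68 × √DE) − 1.96)

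| ICC | Class enrolled (analysed) | DE | Type I error if ignored | Power if modelled |
|---|---|---|---|---|
| 0.01 | 10 (7.6) | 1.066 | 5.8% | 77.7% |
| 0.01 | 15 (11.4) | 1.104 | 6.2% | 76.2% |
| 0.02 | 10 (7.6) | 1.132 | 6.5% | 75.2% |
| 0.02 | 15 (11.4) | 1.208 | 7.5% | 72.5% |
| 0.05 | 10 (7.6) | 1.330 | 8.9% | 68.3% |
| 0.05 | 15 (11.4) | 1.520 | 11.2% | 62.5% |

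At ICC 0, DE is 1 and both columns return to 5% and 80.2%.

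**Step 4: active arm versus control.** If only one arm is clustered, the variance rises by (DE + 1)/2. At ICC 0.02 with 15 enrolled per class this is (1.208 + 1)/2 = 1.104, which gives a type I error of 6.2% and power of 76.2%.

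**Step 5: Bonferroni.** The plan applies this correction but does not state the number of tests. Assuming three (α = 0.0167, critical value 2.394), the type I error for ERS+SMS versus ERS if clustering is ignored is 2.0% to 2.3%, 2.4% to 2.9% and 3.8% to 5.2% at the three ICCs. The absolute error falls, but the ratio to the nominal level does not: at ICC 0.02 and 15 per class it is 2.94/1.67 = 1.76, against 7.45/5 = 1.49 without the correction.

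**The case against.** The strongest reply has four parts.

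- **Group delivery of ERS is not stated.** Only the SMS sessions are called group-based. For ERS the article gives a fixed trainer and exercises adapted to each person's functional level. Classes are a natural inference, but if ERS is less clustered than SMS, inflating both arms equally overstates the effect. This stands, and the table should be read with it in mind.
- **The correlation may be small when it matters.** The main assessment is "month 22 (18 months post intervention) which will be the main outcome assessment", and similarity built up in class may have faded by then. The Study interventions section can also be read as saying that trainers serve both active arms. The trainer part of the correlation would then partly cancel in ERS+SMS versus ERS, though the class part would not. This stands as a limit on size.
- **This is a condensed article.** The final random-effects specification is often left to an analysis plan, and the authors do recognise the clustering. That would answer a complaint about missing detail. It does not answer a stated rule that permits omission beside a firm commitment for centre and couples, nor a stated power that depends on independence.
- **Other model features may recover power.** Baseline or repeated-measures adjustment could do so, though the Sample size section claims none. It would not restore type I error control if clustering is ignored.

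A reader might also infer that the choice of random effect will be made after seeing the results. The article does not support that. It does not say when the choice is made, and the Randomisation and blinding section keeps the statistician blind to allocation until the analysis is complete.

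**Conclusion.** The concern holds in limited form. The main model leaves clustering in the two active arms optional and its unit unnamed, and the stated 80% power assumes independent participants. Any positive class or trainer ICC therefore makes the ERS+SMS versus ERS test anticonservative if the term is omitted, or takes power below the claim if it is included.

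The step 3 figures are illustrative only. They rest on assumed ICCs and class sizes, equal clustering in both active arms and an unadjusted 5% level. Lower ICCs at month 22, shared trainers or less clustered ERS delivery would shrink the effect. The documents do not support reading the table as the trial's actual error rate, or concluding that the trial is underpowered by a known amount.

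**What to change.** In Data and statistical analysis, turn the permission into a commitment. A random effect for exercise class (or trainer, with the unit named) will be included in ERS and ERS+SMS. Use a partially nested model in which control participants are unclustered, unless their two health advice meetings are run in fixed groups. Choices such as arm-specific residual variances or small-sample degrees of freedom are reasonable options, but this point does not depend on them.

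Record class and trainer identifiers for every participant. The Trial status section reports fewer than 250 enrolled and none through the intervention at submission, so this could still be done.

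In Sample size, say that 80% holds only under independence and restate power over a stated range of ICC and class size.

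The cost is slightly wider confidence intervals, a less favourable stated power and two extra identifiers in the dataset. No extra participants are needed. The change makes the stated power honest but does not bring it back to 80%.
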